### Statistical analysis

Analyses will be done in R [35] and Stata 14.0 (Stata Corp., TX, USA). Baseline characteristics will be computed as proportions or median (interquartile range (IQR)), as appropriate, by arm in each of the two stages of the trial. Any variables that show imbalances will be adjusted [33] for when analysing the trial outcomes at the end of the second stage. We will assume that the two stages of the trial are independent [26] and will proceed to carry out a test of the null hypothesis of no difference in effectiveness of each intervention compared to the SOC. We will do this by analysing data from the first stage first followed by interim decisions to drop arms; then we will conduct and analyse data from the second stage (no overlap of participants from the first stage). Analysis of the whole trial will then be based on combined *p* values from both the first stage and the second stage using the weighted inverse normal (WIN) method [36] for arms that are not dropped at interim. A weighted average of the log (risk ratio (RR)) will be computed for the whole trial using estimates from each trial stage. All analyses will be by intention-to-treat taking as the denominator the number of women who were eligible and take into account the clustered design.

Given the small number (six) of clusters per arm in the first stage, analysis will be by cluster-level summaries using mean of proportion of male partners per clinic day who link to care or prevention in each arm [33]. The proportion of male partners who link into care or prevention will be computed per clinic day for each arm with number of men achieving the primary outcome and the number of women eligible and recruited in ANC on enrolment day as denominator. A log transformation of the clinic day proportions will be applied if a positive skew is observed [33]. The geometric mean of clinic day proportions in each of the five intervention arms will be compared to the SOC arm using an unpaired *t* test [33]. An estimate of the RR and a 95% CI will also be computed for each comparison by dividing the geometric mean of proportions in each intervention arm and the geometric mean of proportions in the SOC arm [33].

This analysis involves more than two comparisons with a single control arm which can lead to higher than the specified FWER or significance level. Therefore, Dunnett’s test [29] will be applied to the *t*-statistics generated from the unpaired *t* test to control the stage-wise FWER. Final decision-making at interim analysis will compare the Dunnett-corrected *p* values to stage 1 FWER of 0.2. The first of the three-part criteria for dropping trial arms will then be considered after examining final *p* values at the end of the first stage (interim analysis). Although sample size will be re-calculated at the end of stage 1, the total number of clinic days per arm is still presumed to be small for stage 2. Since the two stages are assumed to be independent, cluster-level summaries approach analogous to stage 1 analysis will also be followed in stage 2 comparing intervention arms that proceed to stage 2 with the SOC arm. A detailed analysis plan will be developed to guide analysis of the trial.

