### Primary and secondary outcomes

The primary outcome is the proportion of male partners of ANC attendees who test for HIV and link into HIV care or prevention within 28 days of enrolling the woman (Fig. 3). Thus, the primary outcome is defined as presentation of the male partner at the MFC with a used self-test kit (if in the intervention arm) or undergoing spot HIV testing with a study HIV counsellor within 28 days AND being referred for HIV care if HIV positive or VMMC if HIV negative and uncircumcised. There are four secondary outcomes: the proportion of male partners who test for HIV within 28 days (as reported by the woman); the proportion of women who accept to participate in their allocated trial arm; risk of serious adverse events (SAEs) in men and women in the study; and the total cost of implementing each trial arm. All outcomes will be analysed at cluster level (see the ‘Statistical analysis’ section).

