### Outcome measurement

All male partners who present at the MFC in the SOC arm will be offered a single finger-prick HIV test with Determine 1/2™ as per Malawi national testing algorithm. An HTS counsellor will re-read a used self-test kit if the participant returns one as evidence of self-testing in the intervention arms. Participants who return with unused self-test kits or without self-test kits will be requested to self-test in the presence of the counsellor. All HIV results will be recorded on a data form followed by confirmation of HIV-positive results in parallel using Determine 1/2™ and Uni-Gold, with facilitated linkage to HIV care. All men who test HIV negative and report to be uncircumcised will be offered VMMC to be conducted by Population Services Internal (PSI). Thus, measurement of primary outcome includes evidence of an HIV test, confirmatory testing, and referral to HIV care or VMMC as appropriate within 28 days of the woman being recruited.

The secondary outcome of HIV testing among male partners will also be measured though proxy reporting by the woman using audio computer-assisted self-interview (ACASI) during her next ANC visit 4 weeks later. Participation in the allocated trial arm will be measured by computing the proportion of women who accept to participate after receiving trial-arm-specific information using the denominator of the total number of women who are eligible. All women will be asked to report any adverse events through ACASI at their next ANC visit while men who present to the MFC will be asked to report any adverse events. A costing tool validated in urban Blantyre [31] will be used to capture the costs associated with providing the service in each trial arm. The cost and outcome data will be used to estimate the cost per male partner tested for HIV, and cost per HIV-positive male identified through all SOC and intervention arms.

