### Sample size considerations

A modification of the formula for sample size calculation for a MAMS design for binary outcomes [32] was made based on the methodology for CRTs [33] to identify each stage of the trial. We assume that each ANC day will have at least 40 women attending for the first time, 90% will satisfy the eligibility criteria and at least 60% will consent to participate, so having a cluster size of at least 21. We also assume that in the SOC arm 25% of men will satisfy the definition of the primary outcome [34]. For the first stage, six ANC days per arm (36 days in total) would be needed to detect an absolute difference of 15% in linkage compared to 25% in the SOC arm using a FWER of 0.2 with 80% pair-wise power and a coefficient of variation (*k*) of 0.10 [21]. In general, under the stated assumptions the trial has 80% chance of detecting a 1.6-fold increase in testing and linkage within 28 days compared to SOC at 5% significance level. Sample size for the second stage will be re-calculated based on empirical estimates at interim analysis with FWER of 0.1 and 80% power.

Very little clustering within ANC days is expected, hence we have assumed that *k* = 0.10 (intraclass correlation coefficient = 0.003). The simulation study assumed that *k* = 0.2 and differs with the final design in this respect resulting in six and seven clusters per arm in the final design and the simulation, respectively. A larger than conventional (0.05) FWER of 0.2 and 0.1 for stage 1 and stage 2, respectively, may lead to erroneously taking forward an ineffective intervention. However, given that this is a phase II trial this is not a major concern as it guards against dropping interventions that may otherwise prove to be effective in a larger, phase III trial. A more conventional pair-wise power of 0.8 was chosen to ensure that there is a high chance of taking forward most of the efficacious interventions from stage 1.

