### Adaptations at interim analysis (end of stage 1)

Interim analysis at the end of stage 1 will assess whether any of the five intervention arms should be dropped as recommended by an independent Data Monitoring and Safety Board (DSMB) based on a three-part criteria. First, an arm whose statistical comparison to the SOC arm yields a *p* value > 0.2 will be considered for dropping for futility. Second, any intervention arm with a *high* incidence of SAEs, i.e. grades 3, 4 or 5 (Table 3) compared to SOC will be considered for dropping. It is at the discretion of the DSMB to decide, based on absolute number of SAEs in each intervention trial arm, whether they are high or not. Such an observation and recommendation will then be shared with the investigators who will make the final decision. Thirdly, an arm may be maintained after taking into account the costs associated with providing the service in light of the *p* value from statistical analysis. For this cost analysis, we will provide the DSMB estimates of the incremental cost per male partner tested, and incremental cost per HIV-positive male identified through the intervention arms in comparison to the SOC arm. The investigators will access the first-stage data only after the last follow-up visit for participants has occurred in order to perform interim analysis. The CRT extension to the Consolidated Standards of Reporting Trials (CONSORT) [37] will be followed when reporting the data.

**Table 3 Tab3:** Adverse event grading

Grade 1 (Mild)	Grade 2 (Moderate)	Grade 3 (Severe) (within 30 days)	Grade 4 (Potentially life-threatening) (within 30 days)

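### One denominator of eligible women for all analyses does not fit woman-reported testing and SAE risk, which are observed only in women who return and men who attend

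*Protocol article*

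**What the plan says.** The Statistical analysis section sets one rule: "All analyses will be by intention-to-treat taking as the denominator the number of women who were eligible". Primary and secondary outcomes sends the secondary outcomes to the same place: "All outcomes will be analysed at cluster level (see the ‘Statistical analysis’ section").

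The next paragraph of Statistical analysis, describing the primary outcome, uses a narrower set: "the number of women eligible and recruited in ANC on enrolment day as denominator".

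The testing outcome is "the proportion of male partners who test for HIV within 28 days (as reported by the woman"). Outcome measurement says it is obtained by "proxy reporting by the woman using audio computer-assisted self-interview (ACASI) during her next ANC visit 4 weeks later". For safety, women report adverse events "through ACASI at their next ANC visit while men who present to the MFC will be asked to report any adverse events".

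Eligible is a wider group than recruited. Sample size considerations assumes that "at least 60% will consent to participate", and Outcome measurement takes eligible women as the denominator for acceptance of the allocated arm.

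At the interim analysis the DSMB decides whether SAEs are high "based on absolute number of SAEs in each intervention trial arm".

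**The concern.** The numerator and the denominator come from different groups. A woman who declined, or who enrolled but did not return, has no interview. She still sits in the denominator and can add nothing to the numerator, so she has the same effect as a woman whose partner did not test and who had no SAE.

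This is reasonable for the primary outcome, where presenting at the clinic is itself part of the outcome. It is not reasonable for a question that was never asked, and for SAEs it lets non-observation pass for safety. Absolute levels come out too low. If consent or return differs between arms, that difference can appear as a difference in testing or in safety.

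A related but separate problem affects the interim safety criterion. A raw count does not use the denominator at all, but it grows with the number of people asked, and men are asked only if they attend.

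**Working it through.** **The plan's own figure.** Inputs from Sample size considerations: 40 first attenders per clinic day, 90% eligible, 60% consenting.
- Eligible: 40 × 0.90 = 36.
- Recruited: 36 × 0.60 = 21.6, which agrees with the stated cluster size of at least 21.
- Eligible but not enrolled: 36 − 21.6 = 14.4 per day, and 14.4 / 36 = 40%.

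**Share observed by interview.** The document gives no return rate; 70-90% is an assumption.
- Denominator of eligible women: consent × return = 0.60 × 0.70 = 0.42 to 0.60 × 0.90 = 0.54.
- Denominator of eligible and recruited women: return alone = 0.70 to 0.90.

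These shares are also the highest value that the woman-reported testing proportion can reach.

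**Understatement, if women not seen resemble those seen.** The factor is 1 / share observed.
- Eligible: 1 / 0.54 = 1.9 to 1 / 0.42 = 2.4.
- Eligible and recruited: 1 / 0.90 = 1.1 to 1 / 0.70 = 1.4.

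Illustration at an assumed 80% return:

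| True value (assumed) | Eligible (× 0.48) | Eligible and recruited (× 0.80) |
|---|---|---|
| Testing 50% | 24% | 40% |
| SAE risk 2% | 0.96% | 1.6% |

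**Risk ratio when the true ratio is 1.** All arm-specific rates are assumptions.
- Equal consent and equal return: apparent ratio 1.00 on either reading.
- Consent 60% v 75%, return 80% in both, true testing 50%: the eligible denominator gives 0.5 × 0.60 × 0.80 = 24% v 0.5 × 0.75 × 0.80 = 30%, ratio 1.25. The recruited denominator gives 40% v 40%, ratio 1.00.
- Equal consent, return 70% v 90%: 0.90 / 0.70 = 1.29 on either reading.

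**People asked about SAEs, per arm in stage 1.** Six clinic days × 21 = 126 recruited women, with the plan's 25% v 40% linkage.
- Men asked: 126 × 0.25 = 31.5 v 126 × 0.40 = 50.4, ratio 1.6.
- Women asked, with equal return: 126 × 0.70 = 88.2 to 126 × 0.90 = 113.4 in each arm.
- Both together: at 70% return, 119.7 v 138.6, ratio 1.16; at 90% return, 144.9 v 163.8, ratio 1.13.

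**The case against.** **The narrower denominator may have been meant throughout.** The same section uses eligible and recruited women for the primary outcome, the sample size is built on recruited women, and the safety outcome is defined for men and women in the study, which a woman who declined is not. This has force. It removes the consent factor, brings the understatement down to 1.1- to 1.4-fold and makes the 24% v 30% example disappear. It does not remove the problem, because recruited women who do not return still count as non-events.

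**Handling of missing interviews belongs in the analysis plan, which is announced.** It is also true that the article nowhere says women without an interview are scored as not tested or free of SAEs; that is the arithmetic consequence of the rule. But the denominator is not left open. It is stated for all analyses, with no exception for these outcomes.

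**Testing is not known from the interview alone.** The Discussion mentions returned kits as well as proxy report. The secondary outcome is nevertheless defined as what the woman reports, and for that outcome the interview is the only source given.

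**Consent need not vary by arm.** A reader might infer that it is expected to, because arm-specific information precedes consent and acceptance is a secondary outcome. The document makes variation possible but does not state it, and the 60% v 75% contrast is illustrative.

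**The DSMB has discretion, and counts do not use the denominator.** Both are correct. The criterion is framed as incidence compared with the standard-of-care arm, and the Discussion expects SAEs mainly from violence to women, who are asked by the same route in every arm. A reader might infer that an effective arm would show 1.6 times the SAEs. That ratio concerns men asked; for women and men together the number asked differs by about 1.13 to 1.16.

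**Conclusion.** The concern holds on both readings of the denominator. With an assumed 70-90% return, the interview covers 42-54% of the denominator if all eligible women are meant, and 70-90% if eligible and recruited women are meant. The corresponding understatement is 1.9- to 2.4-fold or 1.1- to 1.4-fold. Those factors assume that women not seen have similar testing and SAE risk to those seen, which cannot be checked from the document. The larger factor should not be quoted alone, since the section contains both denominators.

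Bias in the risk ratio is conditional: it needs a difference between arms in consent (literal reading only) or in return (either reading). If neither differs, only the absolute levels are wrong.

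The SAE counts are a separate and smaller matter. They partly reflect how many people were asked, most clearly for men.

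These are secondary outcomes, and neither the primary comparison nor the p-value criterion for dropping arms depends on them. The change is still worth making, because one of them is the safety outcome and SAEs are one of the three interim criteria.

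**What to change.** 1. Reconcile the two denominators in Statistical analysis for the primary outcome: eligible, or eligible and recruited.
2. Keep eligible women as the denominator for acceptance of the allocated arm.
3. For woman-reported testing and women's SAE risk, report among women with a completed interview. Report men's SAE risk separately, among men asked at the male-friendly clinic.
4. Show interview completion by arm.
5. Add bounds over all recruited women, with missing counted as not tested or no SAE as one bound and the opposite as the other.
6. Give the DSMB the number of people asked and SAEs per 100 asked beside the absolute counts, with women and men separate.

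The cost is a few sentences and one table; no new data are needed. The drawback is that the estimate among women interviewed conditions on returning after randomisation and may be selective. The bounds do not cure this, but they show how much it could matter.

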**Methods:**

A phase II, adaptive, multi-arm, multi-stage cluster randomised trial, randomising antenatal clinic (ANC) days to six different trial arms. Pregnant women accessing ANC in urban Malawi for the first time will be recruited into either the standard of care (SOC) arm (invitation letter to the male partner offering HIV testing) or one of five intervention arms offering oral HIV self-test kits. Three of the five intervention arms will additionally offer the male partner a financial incentive (fixed or lottery amount) conditional on linkage after self-testing with one arm testing phone call reminders.

Assuming that 25% of male partners link to care or prevention in the SOC arm, six clinic days, with a harmonic mean of 21 eligible participants, per arm will provide 80% power to detect a 0.15 absolute difference in the primary outcome. Cluster proportions will be analysed by a cluster summaries approach with adjustment for clustering and multiplicity.

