**Fig. 2 Fig2:**
[figure not shown]
Randomisation, recruitment, and outcome evaluation. Each cluster (antenatal clinic day) is randomised to any of the six trial arms. All women attending their first antenatal clinic are briefed about the general purpose of the trial without receiving trial arm-specific information. Women then undergo one-on-one eligibility screen and arm-specific information. Women who are eligible and accept to participate are then given a male partner invitation letter alone or with two self-test kits to take home

Field workers will enrol women into one of the six study arms on the morning of each ANC day after receiving the randomisation allocation for that ANC day (see Additional file 1). Women will receive study information in a group while in the ANC waiting area followed by one-on-one eligibility assessment and subsequent recruitment. Study information given during group sessions will not reveal details of arm-specific procedures to avoid potential non-participation associated with knowledge of procedures for each arm. All women who show interest at this stage will provide unwritten consent to participate by show of hands followed by written or witnessed thumb-print consent.

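### The analysis section gives two incompatible denominators for the primary outcome: all eligible women, and eligible women who were recruited

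*Protocol article*

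**What the plan says.** The Statistical analysis section contains both rules. Its first paragraph closes with a general statement that every analysis follows intention-to-treat, "taking as the denominator the number of women who were eligible". The second paragraph, which defines the clinic-day proportion for the primary outcome, uses "the number of women eligible and recruited in ANC on enrolment day as denominator".

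Other sections show that the two groups are not the same:

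- Outcome measurement defines acceptance as "the proportion of women who accept to participate after receiving trial-arm-specific information using the denominator of the total number of women who are eligible". The gap between eligible and accepting women is itself an outcome.
- The Fig. 2 legend gives the order of events: "Women then undergo one-on-one eligibility screen and arm-specific information". It continues: "Women who are eligible and accept to participate are then given a male partner invitation letter alone or with two self-test kits".
- Sample size considerations starts from at least 40 first-time attenders per day, of whom 90% are eligible, and adds "at least 60% will consent to participate, so having a cluster size of at least 21". The 21 is therefore a count of recruited women.
- The abstract describes the same 21 differently: "with a harmonic mean of 21 eligible participants, per arm".

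**The concern.** Both sentences govern the primary outcome, and an analyst cannot follow both. A later analysis plan would have to depart from one of them, so this is a conflict between stated rules and not a detail left for later.

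The choice matters because of when women accept. They learn whether the offer is a letter alone, kits, cash, a lottery or a reminder call before they agree to take part. The recruited group is therefore formed after the allocation is known, and its size and make-up may differ by arm. An eligible-women denominator is not affected by that decision.

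The clinic-day proportion feeds the risk ratio and the Dunnett-corrected stage 1 p value. That p value is the first of the three criteria for dropping an arm, it enters the combined stage 1 and stage 2 test, and stage 2 is sized from interim estimates. An unresolved denominator could change which arms continue, and it leaves room to choose after the data are seen.

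**Working it through.** **Inputs.** From Sample size considerations: at least 40 attenders per day, 90% eligible, at least 60% consenting, 25% in standard of care, a 15-point difference, *k* = 0.10, six days per arm, FWER 0.2. Assumed here: acceptance rates by arm, which the article does not give. Partners of decliners are counted as not linked, because only accepting women receive the letter or kits.

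**Step 1: reproduce the plan's figures.**
- Eligible per day: 40 × 0.90 = 36. Recruited per day: 36 × 0.60 = 21.6, so the stated 21 is reproduced as recruited women.
- ICC: 0.10² × 0.25 / 0.75 = 0.0033, as stated.
- Clusters per arm: c = 1 + (z_α + z_β)² [p0(1 − p0)/m + p1(1 − p1)/m + k²(p0² + p1²)] / (p0 − p1)². With m = 21 and an unadjusted two-sided α of 0.2, c = 5.52, rounded up to 6. With *k* = 0.2 it gives 6.86, rounded up to the stated 7. The stage 1 size thus fits the recruited denominator.

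**Step 2: equal acceptance.** Rate among eligible = acceptance × rate among recruited. If 25% and 40% are rates among recruited women and acceptance is 60% in both arms:
- 0.60 × 0.25 = 0.15 and 0.60 × 0.40 = 0.24.
- The risk ratio is 0.24 / 0.15 = 1.60, the same as 0.40 / 0.25. The difference goes from 15 to 9 points, which is a change of scale.

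**Step 3: unequal acceptance, with identical 25% linkage among recruited women (risk ratio 1.00).** The last column is the approximate chance of crossing the stage 1 limit on the eligible denominator. It uses a normal approximation with six days per arm, m = 36, *k* = 0.10 and a two-sided Dunnett critical value of 1.977 (five comparisons, 30 df).

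| Acceptance, SOC v intervention | Rates among eligible | Risk ratio | Chance of crossing |
|---|---|---|---|
| 60% v 70% | 15.0% v 17.5% | 1.17 | 10% |
| 60% v 80% | 15.0% v 20.0% | 1.33 | 26% |
| 60% v 90% | 15.0% v 22.5% | 1.50 | 48% |

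The last row in full: variance = [0.15 × 0.85/36 + 0.225 × 0.775/36 + 0.01 × (0.15² + 0.225²)] / 6 = 0.00152; 0.075 / √0.00152 = 1.92; Φ(1.92 − 1.977) ≈ 0.48.

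The reverse also occurs. With equal 15% rates among eligible women and 60% v 90% acceptance, the rates among recruited women are 25% and 0.15 / 0.90 = 16.7%, a risk ratio of 0.67.

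**Step 4: power on the eligible denominator, equal 60% acceptance.** The non-centrality is 2.476 for recruited women (m = 21.6) and 2.273 for eligible women (m = 36). Power against 1.977 goes from 69% to 62%. This holds *k* at 0.10, although the eligible rate also carries day-to-day variation in acceptance. If acceptance has its own between-day coefficient of variation of 0.10 or 0.20 (assumed, independent of linkage), power is about 58% or 49%.

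**The case against.** The best defence is that the intended denominator can be recovered. The sentence that defines the clinic-day proportion is the more specific of the two, and it says recruited. The sample size counts consenting women, and the 28-day clock starts when the woman is enrolled, so it has no starting point for a decliner. The abstract's use of eligible for the 21 suggests loose shorthand, which may also explain the intention-to-treat sentence. This makes recruited women a defensible reading. It does not settle the matter, because Outcome measurement uses eligible in its strict sense and the general sentence claims to cover all analyses.

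The article also goes some way to handle selection. Group sessions withhold arm details, and acceptance by arm is a secondary outcome, so differential acceptance would be visible. The protection is partial, because one-on-one arm information still comes before acceptance.

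Three stronger readings are tempting but unsupported:

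- *That the choice does create or remove an effect.* It does so only if acceptance differs by arm, and no rates by arm are given. Trial status reports 800 participants in 32 clusters, or 25 per day, about 69% of the planned 36 (itself a minimum). If standard of care were at 60%, the intervention arms would average about (25 − 21.6/6) × 6/5 = 25.7 per day, or 71%, a mean factor near 1.19. A single arm could still be higher.
- *That the eligible denominator invalidates the 25% v 40% assumption.* The 25% comes from a cited source, and its denominator cannot be established from the article. Only the 21 is clearly a count of recruited women.
- *That all eligible women is the only correct choice.* It folds acceptance into the primary outcome and so asks a somewhat different question.

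**Conclusion.** The contradiction stands. The primary outcome has two stated denominators, 36 and about 21.6 women per day on the plan's figures, and the smaller group is formed after the arm is revealed. With equal acceptance the risk ratio does not depend on the choice. With acceptance of 60% against an assumed 70% to 90%, a risk ratio of 1.00 among recruited women is 1.17 to 1.50 among eligible women. At six clusters per arm, that is enough to affect the comparison with p = 0.2. These sizes rest on the assumed acceptance rates and on counting decliners as not linked. No single power cost can be given: 62% on the eligible denominator is a best case, because it ignores daily variation in acceptance. The article does not show that any bias has occurred.

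**What to change.** Before the interim analysis, reconcile the two sentences to one named primary denominator and pre-specify the other as a sensitivity analysis, read beside acceptance by arm.

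- If all eligible women are primary, say that decliners count as not linked. This is the choice that matches the stated intention-to-treat principle.
- If recruited women are primary, remove or qualify the intention-to-treat wording and acknowledge that selection can occur after the arm is revealed.

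State the cluster size and target rates on the chosen denominator, carry it into the stage 2 re-calculation, and correct the description of the 21 as eligible in the abstract.

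The cost is wording and one extra analysis. Eligible counts are already needed for the acceptance outcome, so no new data are required. Making eligible women primary would lose some power, by an amount that depends on how much acceptance varies from day to day. With 32 of 36 stage 1 clusters already covered, that loss could be offset only in stage 2.

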**Fig. 1 Fig1:**
[figure not shown]
Schema of the phase II, adaptive, multi-arm, multi-stage cluster randomised trial. A two-stage, multi-arm, multi-stage (MAMS) trial design starting with six arms in the first stage. At interim analysis (end of first stage) some trial arms may be dropped, with recruitment to the remaining arms aiming to narrow down to a few arms that may be carried forward to a definitive (phase III) trial

Analysis of second stage (end of trial) data will potentially lead to a definitive study (phase III) involving arms that show promise at the end of the second stage. A sample size of 36 ANC days (six per arm) will be required for the first stage (see the ‘Sample size considerations’ section below for justification). In order to control the family wise error rate (FWER) at the specified significance level (*α* = 0.2) for the five comparisons with the SOC arm, Dunnett’s test [29] will be applied.

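### Dunnett's test, read as single-step, is valid; the step-down version gives the same FWER guarantee and passes more effective arms, with a modest gain under the plan's own rates

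*Protocol article*

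**What the plan says.** The Design section, in the text after Fig. 1, introduces Dunnett's test for the five comparisons with SOC: "In order to control the family wise error rate (FWER) at the specified significance level", with alpha set at 0.2. The Statistical analysis section applies the test to the unpaired t statistics to control the error rate within each stage, and adds: "Final decision-making at interim analysis will compare the Dunnett-corrected" p values with 0.2. Stage 2 is to be analysed in the same way. Its sample size is to be "re-calculated based on empirical estimates at interim analysis with FWER of 0.1 and 80% power". Whole-trial p values come from a weighted inverse normal combination of the two stages.

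Sample size considerations gives the purpose. The lenient error rates are meant to avoid losing effective interventions, and the pair-wise power of 0.8 was chosen "to ensure that there is a high chance of taking forward most of the efficacious interventions from stage 1".

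Under Design and under Adaptations at interim analysis, a p value above 0.2 puts an arm up for consideration for dropping, alongside serious adverse events and costs. Dropping is not automatic.

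**The concern.** Single-step Dunnett compares every arm, including the second to fifth best, with the critical value for the maximum of five comparisons. Once the best arm has passed, the null hypothesis that all five arms equal SOC has been rejected. The remaining arms can then be judged against the maximum of four, then three, two and one. Step-down Dunnett does this under the same strong control of the FWER. Its first step is identical, so whatever single-step rejects, step-down also rejects.

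The plan accepts an FWER of 0.2 to protect effective arms, but single-step leaves part of that allowance unused as soon as some arm works. At stake is the number of effective arms that clear the statistical criterion at the interim and, by analogy, in stage 2.

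**Working it through.** **Inputs, from Sample size considerations unless noted.**
- SOC rate 0.25: "in the SOC arm 25% of men will satisfy the definition of the primary outcome".
- Effect and clusters: "six ANC days per arm (36 days in total) would be needed to detect an absolute difference of 15% in linkage", so 0.25 v 0.40 with 6 days per arm.
- Cluster size 21: "so having a cluster size of at least 21".
- Error rate and variation: "using a FWER of 0.2 with 80% pair-wise power and a coefficient of variation" k = 0.10.
- Equal allocation to six arms (Randomisation and recruitment flow), so the comparisons with SOC have correlation 0.5.
- Intervention rates 0.29, 0.30, 0.31, 0.32 and 0.40 (Table 2).
- Sidedness is not stated. The null of no difference suggests two-sided, which is used here.

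**The plan's own figure.** The cluster-trial formula is c = 1 + (z_alpha + z_beta)² × V/(p1 − p0)², with V = p0(1−p0)/m + p1(1−p1)/m + k²(p0² + p1²).
- V = 0.1875/21 + 0.24/21 + 0.01 × (0.0625 + 0.16) = 0.00893 + 0.01143 + 0.00223 = 0.02258, and V/0.15² = 1.004.
- Two-sided alpha 0.2 without Dunnett: 1 + (1.282 + 0.842)² × 1.004 = 5.52, so 6 days. With k = 0.2 the result is 6.86, so 7. Both stated counts are reproduced.
- Two-sided Dunnett (critical z 1.915): 1 + (1.915 + 0.842)² × 1.004 = 8.63, so 9 days.
- Pair-wise power at 6 days under single-step two-sided Dunnett: SE = √(0.02258/6) = 0.0613 and 0.15/0.0613 = 2.445, so power is Φ(2.445 − 1.915) = 0.70.

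**Two-sided critical values, pooled variance, 30 df.**

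| FWER | Single-step, every arm | Step-down, largest to smallest statistic |
|---|---|---|
| 0.2 | 1.98 | 1.98, 1.90, 1.78, 1.62, 1.31 |
| 0.1 | 2.34 | 2.34, 2.25, 2.15, 1.99, 1.70 |

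**Simulation.** There were 100,000 stage 1 trials per scenario. Day-level true proportions had SD k × mean, counts were binomial with 21 women per day, and there were 6 days per arm. The rates below are for crossing the threshold at FWER 0.2.

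| Scenario | Single-step | Step-down |
|---|---|---|
| Table 2 rates, arms 2 to 6 | 10/13/17/21/69% | 14/18/21/26/70% |
| Table 2 rates, mean arms passing | 1.29 | 1.49 |
| Table 2 rates, at least one arm | 0.74 | 0.74 |
| All five at 40%, each arm | 65% | 75% |
| All five at 40%, all five pass | 29% | 56% |
| Four at 40%, one null: each effective arm | 66% | 73% |
| Four at 40%, one null: null arm | 3% | 10% |
| Global null, FWER | 0.20 | 0.20 |

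No simulated trial had an arm pass under single-step and fail under step-down. With one, three or four arms at 40% and the rest null, the step-down FWER was about 0.17, 0.12 to 0.13 and 0.10, all below 0.2. With all five at 40%, separate 10-df t tests gave about 62–64% v 74–75% per arm, and k = 0.2 gave 53% v 63%. One-sided tests showed the same pattern (79% v 88%).

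Table 2's own drop column cannot show which version of Dunnett was meant. It was not reproduced at 6 or 7 days per arm with unadjusted, single-step or step-down rules.

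**The case against.** The strongest reply is that nothing here is an error. Single-step Dunnett does what the plan asks of it, which is to control the FWER within each stage. That stands: this is an improvement at the plan's own error level. The article also never says single-step and announces a detailed analysis plan. The reading rests on the ordinary meaning of the test's name, which is reasonable but inferred.

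Three stronger readings are tempting, and the document does not support them.
- *Effective arms are dropped.* A p value above 0.2 only leads to consideration beside safety and costs, so the percentages are threshold-crossing rates and not retention rates.
- *The extra power costs nothing in error.* The guaranteed bound is the same, but the actual error is higher when other arms work: one null arm beside four effective ones passes 10% of the time instead of 3%.
- *The large gain is the expected one.* All five arms at 40% is not the plan's scenario. Under Table 2 the only arm at the design effect gains about 1 point. The chance of at least one success, which Trial simulation takes as its target, does not change. The gains of 4 to 5 points fall on arms whose effects are 4 to 7 points, and these still pass only 14 to 26% of the time.

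For stage 2 no reliable gain can be stated. The number of days and of surviving arms is unknown, and whole-trial inference uses the combined p values, not a stand-alone stage 2 test.

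**Conclusion.** The point holds as a low-cost improvement. Read as single-step, the planned test is valid, but the step-down version rejects everything it rejects and sometimes more, under the same FWER guarantee. It also fits the stated aim better.

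The gain depends on how many arms work. It is modest under Table 2 (0.2 more arms passing on average) and about 10 points per arm if all five are at 40%. These figures assume two-sided tests, pooled variance, 6 days of 21 women per arm and k = 0.10.

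A reader might infer that the change repairs the power of stage 1. It does not. Six days per arm matches an unadjusted alpha of 0.2, and pair-wise power under two-sided single-step Dunnett is about 0.65 to 0.72. Step-down recovers only part of the shortfall, reaching 75% in its most favourable case here.

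**What to change.** In the Design text after Fig. 1 and in Statistical analysis, name the step-down Dunnett test. Order the absolute t statistics and compare the largest with the critical value for five comparisons, the next with that for four, and so on, stopping at the first failure. Compare the step-down adjusted p values with 0.2 at the interim, and use the same procedure at 0.1 for the arms in stage 2.

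State also that the step-down adjusted stage-wise p values enter the weighted inverse normal combination. This keeps FWER control: each adjusted value is the largest p value over the intersection hypotheses that contain that arm, so combining the two maxima can only be conservative.

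The cost is a few sentences, with no extra clusters or data. Ineffective arms will pass somewhat more often when others work, within the stated FWER, and slightly more arms may enter stage 2. Matching simultaneous confidence intervals are not simple, but the plan reports an ordinary 95% CI for each comparison. The stage 1 power shortfall needs separate attention.
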